## Abstract

**Background:** Degenerative lumbar spinal stenosis is a prevalent condition in adults over the age of 65 and often leads to deconditioning. Although the benefits of surgery outweigh those of conservative approaches, physical rehabilitation may be used to improve function and to minimize the risk of persistent dysfunction. This study protocol was designed to establish the feasibility of a full-scale randomized controlled trial and to assess the efficacy of an active preoperative intervention program on the improvement of clinical parameters and functional physical capacity in patients undergoing surgery for lumbar spinal stenosis.

**Methods/Design:** Forty patients will be recruited and randomly allocated to one of the 2 treatment arms: 6 weeks supervised preoperative rehabilitation program (experimental group) or hospital standard preoperative management (control group). The intervention group will be trained three times per week, with each session aiming to improve strength, muscular endurance, spinal stabilization and cardiovascular fitness. Intensity and complexity of exercises will be gradually increased throughout the sessions, depending on each participant's individual progress. Primary outcomes are level of low back disability and level of pain. Secondary outcomes include the use of pain medication, quality of life, patient's global impression of change, lumbar extensor muscles endurance, maximum voluntary contraction of lumbar flexor and extensor muscles, maximum voluntary contraction of knee extensors, active lumbar ranges of motion, walking abilities, and cardiovascular capacity. Both the primary and secondary outcomes will be measured at baseline, at the end of the training program (6 weeks after baseline evaluation for control participants), and at 6 weeks, 3 and 6 months postoperatively.

**Discussion:** This study will inform the design of a future large-scale trial. Improvements of physical performances before undergoing lumbar surgery may limit functional limitations occurring after a surgical intervention. Results of this study will provide opportunity to efficiently improve spinal care and advance our knowledge of favorable preoperative strategies to optimize postoperative recovery.

**Trial registration:** US National Institutes of Health Clinical Trials registry NCT02258672, 10 February 2014.

**Keywords:** Prehabilitation, Exercise therapy, Lumbar spine, Spinal stenosis, Surgery

\* Correspondence: [contact]

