## Background

Lumbar spinal stenosis (LSS) is one of the most frequent degenerative conditions in older-aged patients [1] and the most common indication for spine surgery in patients older than 65 years [2]. Although several treatment approaches have been suggested in the literature, there is an increasing body of evidence in favor of surgery-related treatment for the management of LSS [3]. For instance, recent evidence shows that decompressive laminectomy/laminotomy alone or combined with fusion for LSS outweighs the effects of non-surgical interventions [3]. In spite of advances in surgical techniques, outcomes following spine surgery are highly variable and advantages following spinal stenosis surgery seem to diminish over time with outcomes becoming similar to those of conservative management at 5 years postoperatively [4]. Furthermore, the frequency of spinal stenosis complex surgeries has increased in the recent years and has been associated with increased costs, risks of complications and resource use, and lower success rates [5, 6].

Although the benefits of surgery outweigh those of conservative approaches for patients with LSS, physical rehabilitation may be used to improve function and to minimize the risk of persistent dysfunction. In fact, a limited course of active physical therapy is initially recommended for patients with LSS [7]. Such a decision may be motivated by the fact that watchful waiting of LSS does not result in catastrophic progressions of neurologic deficits [3]. In addition, there is low-quality evidence suggesting that exercise therapy leads to better short-term outcomes than no exercise with respect to disability, back and leg pain [8]. However, the current scientific knowledge does not provide sufficient evidence to establish clear recommendation for or against the use of physical therapy or exercise as stand-alone treatments for degenerative LSS [7]. Beyond the effectiveness as stand-alone treatments lies the potential adjuvant effects of conservative modalities to surgical outcomes, which are, however, not clearly understood.

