Authors do acknowledge that much debate persists on which surgical approach is the most cost-effective and may also offer favorable long-term outcomes [2]. Development of innovative surgical techniques, combined with efforts to optimize perioperative patients' management have increased the focus on improvement of postoperative outcomes. The "fast-track surgery" multimodal approach, which focuses on enhancing recovery and reducing morbidity by optimizing preoperative and postoperative patient management, has shown to effectively enhance recovery and reduce need for hospitalization while keeping readmission rates unchanged [12, 13]. Similarly, patient activation, defined as one's propensity to engage in positive health, has been identified as an important modifier of the recovery process, leading to better outcomes and increased compliance to physical therapy after lumbar surgery [14]. Santa Mina et al. recently conducted a systematic review investigating the effectiveness of total-body and region-specific prehabilitation interventions for patients awaiting hip or knee arthroplasty, amongst other conditions [13]. The authors reported improved physical function at the preoperative assessment and improved physical function, length of hospital stay, pain and quality of life following surgery, compared with standard care. We conducted a scoping review exploring current practices in perioperative rehabilitation for lumbar spine surgery and identified only one randomized control trial investigating the effects of a preadaptation program. The study, by Nielsen et al., compared the impact of an integrative program of care, combining both preadaptation and early postoperative rehabilitation, to routine procedures for patients undergoing elective surgery for degenerative disease [15]. Despite the reported improvements in postoperative

function, recovery and hospital stay, the pragmatic design of the study does not allow to tease out the effectiveness of individual interventions.

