## Methods/Design

### Design

This study is a randomized controlled pilot clinical trial. It is design to assess the feasibility and efficacy of an active preadaptation programme in improving patients' recovery following a LSS surgery. The primary outcomes are level of low back disability (as measured by the Oswestry Disability Index (ODI) version 2.1a) and level of pain as measured by a Numerical Rating Scale (NRS)). The proposed study protocol has been approved by the institutional review boards of the *Université du Québec à Trois-Rivières* and *Centre de Santé et de Services Sociaux de Trois-Rivières* (CÉR-2014-008-00), where the study will take place. The trial has been registered with the US National Institutes of Health Clinical Trials registry (NCT02258672). Informed written consent will be obtained from each participant before any intervention is initiated.

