### Sample size

Determination of the sample size was guided by time constraints as well as by a thorough analysis of the patients' surgery rate conducted over a 1-year period at the recruitment site in accordance with our inclusion and exclusion criteria [20]. Furthermore, when one of the study goals is to obtain an estimate of variance in an outcome when an important difference between groups has already been identified (meaning that only the variance needs to be estimated), it is suggested that 10 to 20 participants per group is deemed sufficient to inform feasibility and to plan for a larger study [20].

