### **Statistical analysis**

Participants' characteristics will be summarized using descriptive statistics (mean, standard deviation). The equivalence of groups at baseline in terms of demographic and clinical variables will be assessed using independent samples *t* tests for continuous variables and chi-square tests for categorical variables. Following an intention-to-treat principle, estimates of efficacy (Group and Time main effect, as well as Group x Time interactions) will be analyzed using a repeated-measure analysis of variance (ANOVA). The statistical significance level will be set at 5 % and missing data will be analyzed using multiple imputation methods.

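### The protocol counts the Time main effect as an estimate of efficacy, although Time pools both arms across surgery and does not compare them

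*Protocol*

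**What the plan says.** The protocol's Design section describes a randomised pilot to "assess the feasibility and efficacy of an active preadaptation programme". The last paragraph of the Background frames the question as prehabilitation compared with usual care. According to the Interventions section, the preoperative programme is the only thing that differs by allocation.

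The Statistical analysis section gives the protocol's only definition of an efficacy estimate: "estimates of efficacy (Group and Time main effect, as well as Group x Time interactions". These "will be analyzed using a repeated-measure analysis of variance (ANOVA"). A separate sentence adds: "The statistical significance level will be set at 5" %. The three terms are not ranked, and no between-arm contrast is singled out.

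The Abstract and Table 1 give five assessments for the primary outcomes (ODI and pain NRS): two before surgery, and three after it at 6 weeks, 3 months and 6 months. The Eligibility criteria require that every participant is waiting for surgery. The part of the Background on postoperative rehabilitation concludes that surgery mainly reduces pain and gross disability, without a consistent gain in muscle conditioning.

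**The concern.** In a two-arm, five-visit ANOVA the Time main effect tests whether the visit means, averaged over both arms, are equal. It uses no comparison between arms. It takes up whatever both arms share: the effect of surgery, the natural course, and possibly regression to the mean after the decision to operate and the change to mailed forms at 3 and 6 months. None of these is an effect of the randomised programme.

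On the protocol's own account, surgery moves both primary outcomes in the favourable direction. The plan therefore puts the efficacy label on a term that is expected to be non-zero whether or not the programme works. The Discussion section says the pilot is to feed a larger trial. If improvement after surgery were read as support for prehabilitation, that trial would be planned on a signal unrelated to the programme.

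**Working it through.** The documents give no power, effect size, SD or correlation, so there is no stated figure to reproduce. The check asks how often each term would be significant if the programme had no effect at all.

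**Inputs from the protocol.** Total sample 40 (Abstract: "Forty patients will be recruited and randomly allocated to one of the 2 treatment arms"); five visits, two before and three after surgery (Abstract, Table 1); 5 % level (Statistical analysis).

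**Assumed inputs.** Equal allocation, 20 per arm (no ratio is stated); complete data; SD 1 with the same correlation rho between all visits, varied from 0.3 to 0.7; programme effect exactly zero; the same postoperative improvement of d SD in both arms at all three postoperative visits.

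**Formula for Time.** The visit means are (0, 0, -d, -d, -d), with mean -0.6d. The sum of squared deviations is 2 x 0.36d² + 3 x 0.16d² = 1.2d². The noncentrality parameter is lambda = 40 x 1.2d² / (1 - rho), on 4 and (40 - 2) x 4 = 152 degrees of freedom.

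- d = 0.5: 40 x 1.2 x 0.25 = 12, so lambda = 17.1, 24 and 40 for rho = 0.3, 0.5 and 0.7. Power of the Time test: 92.3, 98.4 and 100 %.
- d = 0.3: 40 x 1.2 x 0.09 = 4.32, so lambda = 6.2, 8.6 and 14.4. Power: 46.9, 62.8 and 86.5 %.

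**Simulation of the same ANOVA** (4,000 trials per setting, no programme effect) agrees. Percentage of trials with Time significant:

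| Shared shift d | rho 0.3 | rho 0.5 | rho 0.7 |
|---|---|---|---|
| 0.2 SD | 22 | 29 | 49 |
| 0.3 SD | 47 | 62 | 87 |
| 0.4 SD | 75 | 88 | 99 |
| 0.5 SD | 92 | 98 | 100 |
| 0.75 SD or more | 100 | 100 | 100 |

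In the same trials Group x Time was significant in 4.3 to 5.8 %, whatever the size of the shared shift. Counting either Group or Group x Time as evidence gave about 9 to 10 %.

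**Smaller samples.** The Sample size section says that "10 to 20 participants per group is deemed sufficient to inform feasibility". At d = 0.5, with rho 0.3, 0.5 and 0.7, Time is significant in 85, 95 and 99.7 % of trials with 16 per arm, and in 62, 78 and 95 % with 10 per arm.

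**The Group main effect.** This is a between-arm comparison, but if baseline is one of the five repeated measures it includes a pre-treatment visit. A constant arm difference of delta at the four later visits gives a Group effect of (0 + 4 x delta)/5 = 0.8 delta, a dilution of one fifth.

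**The case against.** The strongest reply is that the parenthesis only names the three standard terms of a two-way repeated-measures ANOVA. The term that carries the programme effect, Group x Time, is among them and keeps its 5 % level. The Background sets a between-arm question, and the Discussion wants to learn how function changes after surgery, for which Time is a proper description. Much of this stands: Time should still be estimated, and the right kind of contrast is already planned. What does not stand is the label, because the text calls Time an estimate of efficacy and nothing else in the protocol withdraws that.

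Three stronger readings are tempting but not supported.

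- A reader might infer that the trial will declare prehabilitation effective in more than 90 % of cases even if it does nothing. The plan has no rule that one significant term establishes efficacy, and the 5 % level is a general sentence. The percentages above are the power of the Time test to detect a real shared change. They would become false efficacy rates only under a decision rule that the protocol does not state.
- A reader might infer that Time is bound to be significant. That depends on the size of the shared change, which the documents do not give; at 0.2 SD the rate is 22 to 49 %. Nor does it extend automatically to the physical measures. They have three visits, and the Background says that surgery does not reliably improve muscle conditioning.
- A reader might infer that the plan repeats the weakness it criticises in the earlier prehabilitation trial, whose design "does not allow to tease out the effectiveness of individual interventions". That criticism concerns a package of preoperative and early postoperative rehabilitation whose parts cannot be separated. Pooling arms over time is a different problem.

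**Conclusion.** The point holds as an error in what the protocol calls efficacy. Time averages both arms across an operation that all participants are due to have, so it is not a randomised comparison of the programme with usual care. The protocol's own Background predicts a Time effect on the primary outcomes without any programme effect.

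The size is conditional. With 40 patients and five visits, Time is significant in 92 to 100 % of trials without a programme effect at a shared 0.5 SD improvement, and in 47 to 87 % at 0.3 SD, against about 5 % for Group x Time. These figures rest on the assumed shift, correlation structure, equal allocation and complete data. The conclusion about the label does not depend on them.

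**What to change.** In the Statistical analysis section, take the Time main effect out of the efficacy estimates and state that change over time is reported descriptively, as the course of recovery.

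State that efficacy is judged from one between-arm contrast, reported with its 95 % confidence interval. This can be Group x Time, which is already planned, or the baseline-adjusted arm difference at a named postoperative visit. With two arms and five visits the overall interaction test has (2 - 1) x (5 - 1) = 4 degrees of freedom and no single interval. If it is chosen, the arm difference in change from baseline should be shown with its interval.

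The Group main effect averaged over all visits, baseline included, should not serve as the efficacy estimate, because the pre-treatment value dilutes it. Naming one contrast also avoids the rate of about 9 to 10 % that arises if either Group or Group x Time may count.

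The cost is a sentence or two of text. No extra patients, visits or data are needed.

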### **Ethical considerations**

Considering that patients are on a waiting list for their surgical intervention, it is possible that the training period will vary from one individual to the next. No intervention presented herein will delay or interfere with the patients' surgical planning. All participants have the right to withdraw from the study at any time and the research team reserves the right to stop the trial if it is believed that there are risks of adverse events or if the patients' condition or symptoms worsen.

### **Discussion**

Despite the development of innovative surgical approaches and efforts being made to optimized treatment plans for the management of low back pain, the role of exercise therapy as an adjunct to operative modalities remains unclear. This pilot study will provide preliminary data that will be used as a 'stepping stone' for a future large-scale clinical study investigating the effects of a prehabilitation program on patients' recovery following spinal stenosis surgery. In addition to the assessment of possible effects and associations that may be worth investigating in a subsequent larger trial, the study will allow for documentation of patient compliance and

satisfaction regarding a prehabilitation protocol based on exercise training.

In a broader perspective, the observations gathered during the pilot study will expand the knowledge related to the functional changes affecting patients after lumbar surgery, allowing for identification of specific components of physical fitness that should be targeted in future prehabilitation protocols. Similarly, it is believed that the results of this study could eventually lead to improvement in the delivery of spinal care. Identification of patients' characteristics likely to respond favorably to prehabilitation will help target the individuals for whom it should be considered to limit symptoms persistence, and post-surgery complications and side-effects.

### Trial status

The trial is currently recruiting participants. Enrollment and trial completion is expected to be finished by the end of 2015.

### Abbreviations

ANOVA: analysis of variance; BDI: Beck Disability Index; CGI-I: Clinical Global Impression - Improvement scale; EQ-5D-3 L: EuroQol-5D-3 L questionnaire; LSS: lumbar spinal stenosis; MSQ: Minnesota Satisfaction Questionnaire; NRS: Numerical Rating Scale; ODI: Oswestry Disability Index; TAT: total ambulation time; TFS: time to first symptoms.

### Competing interests

None of the authors have any competing interests to disclose. None of the funding bodies are involved in or have influence over the design of the study, the interpretation of the results, or the decision to publish the results.

### Acknowledgments

This study was funded by the *Fonds institutionnel de recherche clinique de l'université du Québec à Trois-Rivières* et le *programme de soutien au démarrage de projets de recherche en collaboration CSSSTR-UQTR*.

